## Discussion

One of the main strengths of the More2Sleep study is its multidisciplinary approach, as it assesses two critical domains of children's health: body weight regulation and learning ability. The primary outcomes are complemented by several secondary outcomes expected to provide valuable insights into the mechanisms underlying the effects of sleep extension (e.g., energy expenditure, metabolic risk factors, cognitive performance, and brain function and structure). The findings of the study will provide a better understanding of the potential causal links between short sleep duration, body weight homeostasis, metabolism, and learning ability in children. Another strength is the inclusion of a large sample of school-aged children who sleep less than recommended, which increases our ability to detect a clinically relevant change and enhances the applicability of our findings.

We have designed the intervention (sleep extension and control) to include the same number and frequency of sessions with the family advisor in both groups. The content focusing on providing the whole family with guidance, motivation, and support will help achieve the required sleep extension. Previous studies have shown that collaboration between children and parents is important for adherence to similar behavioral interventions (81, 82). The frequency of meetings will also allow us to monitor adherence, provide support, and add or adjust strategies at home as needed. Combining in-person and virtual sessions can ease the logistical burden on families while still allowing progress to be tracked.

Additionally, the study design includes a dual-compliance assessment of sleep using parental reports and child actigraphy. This is important, as a previous study found that both parents and children tend to overestimate sleep duration, especially the time spent awake at night, compared with objective measures (83). Because parental reporting may be influenced by awareness of the intervention, reported adherence may be biased. However, this potential bias can be assessed using objective actigraphy analyses.

The behavioral nature of the intervention may introduce additional bias. Since the behavioral nature of the intervention precludes blinding of families and the family advisor, this may introduce performance bias if behaviors other than sleep are influenced during the study. To minimize the impact of this bias on our outcomes, both groups will follow a similar schedule of visits and interaction with study staff, and the same family advisor will be involved across groups to ensure consistency in contact and guidance. Furthermore, study staff who will assess outcomes and perform analyses will be blinded to group allocation, and several outcomes will be objectively measured, reducing the risk of detection bias. Nevertheless, it cannot be ruled out that general well-being content in the control group may influence behaviors such as diet, physical activity, or learning.

Another limitation is that even though More2Sleep has a longer duration than previous studies investigating the effect of sleep manipulation on children's weight (20, 21, 23, 24), cognitive functions, and academic performance (30, 31), the timeframe may still be inadequate to detect significant changes in body weight and learning abilities, which are outcomes typically affected on very long timescales.

Another consideration concerns which activities additional sleep may replace. Results from two systematic reviews, mainly focusing on sleep quantity, indicate a negative association between sleep duration and screen time in children and adolescents (84, 85). This highlights that the lack of assessment of screen use in this study may be a potential limitation.

Additionally, several questions remain about the role of sleep in children's health, which are beyond the scope of this study. One is defining the minimum amount of sleep required for optimal health, which in itself can be defined in various ways, for example, in relation to physical or mental performance (86). While guidelines on recommended sleep typically refer to the entire pediatric population within a certain age range, individual sleep needs likely vary widely and can be influenced by inter- and intra-individual factors (86). The importance of sleep quality vs. sleep duration also requires further clarification (30), but measuring sleep quality is more complicated. Although sleep quality will be evaluated in this study using PSG, these measurements will capture only one night's data and may not accurately reflect the child's typical sleep patterns.

Another limitation of this study is the lack of temporal information on which outcome (i.e., body weight or learning) improves first. While we will explore the underlying mechanisms of the potential effects of sleep on body weight homeostasis and learning ability, we will not be able to disentangle the interrelatedness between overweight/obesity and suboptimal cognitive functioning. We expect sleep extension to be accompanied by positive changes in both domains; therefore, we cannot conclude whether improvements in body weight regulation, in themselves (i.e., independent of sleep), may lead to improved cognitive functions, and vice versa. This highlights the need for further research to clarify causal pathways.

## Ethics and dissemination

The study (reference number: H-23063352) has been approved by the Danish Research Ethics Committee on 02 February 2024. Additional protocol amendments are submitted to the committee and updated in ClinicalTrials.gov on an ongoing basis. The study will be conducted in accordance with the ethical principles outlined in the current version of the Declaration of Helsinki (Fortaleza, Brazil, October 2013), the principles of the International Conference on Harmonization E6 Good Clinical Practice (ICH-GCP) R2, and all applicable local regulatory requirements.

All children participating in the main study (visits A, B, and C) will receive a gift certificate per completed visit. All children will receive a commercial activity smartwatch at the end of the 12-week active intervention. Children participating in substudies will receive an additional flexible gift certificate.

While the study intervention poses no direct risks, participation in clinical research may disrupt everyday life, especially for families with young children, thus requiring time for study procedures. Special attention will be paid to the children's responses and reactions throughout the study, and participation will be terminated if a child shows unwillingness to continue.

Certain procedures may carry minor risks. There is a minor risk of slight pain and bruising for blood samples, although local anesthetic patches will be used to minimize discomfort. A maximum of 20 mL of blood is collected from each of the participating children, and 40 mL from children participating in Study I. The DXA scan involves minimal radiation exposure (0.011 mSv), with only one rescan permitted per visit if the initial scan fails.

The DLW method is safe for use in humans of both sexes and all ages (56). The weighed dose of DLW contains a measured enrichment of about 6.6 atomic % ^2^H and 10 atomic % ^18^O. This results in an initial excess body water enrichment of 100–120 ppm for ^2^H, which is <0.2% of the threshold above which side effects and toxicity may manifest. No physiological effects have been detected even at body water enrichments of ∼60% ^18^O (56).

Wearing the actigraphy device, polysomnography equipment, and surface electrodes used in EEG and EMG may cause skin irritation. Additionally, in rare cases, EEG-compatible gel may cause an allergic reaction in particularly sensitive individuals. EEG and EMG are safe for use in children. If skin irritation is observed, electrodes and gel are removed, and these measurements are omitted.

MRI is a non-invasive imaging method with no known biological hazards and has been approved for use in children. To minimize distress and motion, children will be acclimatized to the MRI environment using a scanner simulator. Scanning will be terminated immediately if a child shows signs of discomfort or requests to stop.

Finally, to ensure participant safety, vital signs, including resting blood pressure, heart rate, and body temperature, will be assessed at all main visits (A, B, and C). Potential adverse events will be assessed during the study period. If the child's general condition precludes continuing the study, as determined by the study personnel or the medical expert, participation will be discontinued. Participation will also be discontinued in cases of significant non-compliance, lack of cooperation, or unforeseen events that make the child ineligible to participate. Additionally, all participants are insured in accordance with national legal requirements in the event of injury resulting from study procedures.

Regardless of the outcome, the results of the study will be published in peer-reviewed journals and presented at scientific conferences.

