### Compliance

Compliance will be assessed using both a parent-reported sleep diary that records bedtime, sleep onset time, and wake-up time, and actigraphy data collected via a wrist-worn accelerometer, with the children wearing the accelerometer on the same days as the sleep diary is completed. Compliance is defined as an increase in sleep duration of ≥30 min/night after 12 weeks.

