### Data collection and outcomes

The study involves various visits for participating families, including an information meeting, screening, assessment visits A and B (each spanning over 2 days), visit C, sessions with the family advisor, and additional visits for those participating in substudy-I and substudy-II. Data collection follows standard operating procedures and is detailed in Tables 1, 2. Most data are collected during the active intervention period. Participants who discontinue the intervention will be invited to attend an early termination visit. Participants who withdraw from the study during the active intervention will be invited to attend an early termination visit identical to Visit B, whereas those who withdraw during follow-up will be invited to attend a visit identical to Visit C.

**Table 1 T1:** Overview of visits and assessments for the main study.

Method/assessment	Outcomes	At home	Visit A	At home	Visit B	At home	Visit C
		(Week −1)	(Week 0)	(Weeks 1–11)	(Week 12)	(Weeks 13–37)	(Week 38)
Method/assessment	Outcomes						
Anthropometry and metabolic health							
Anthropometric measurements	BMI z-score		X		X		X
DXA	Fat and lean mass and fat percentage, BMD, and BMC		X		X		X
Fasting blood sample	Clinical biochemistry: cardiometabolic risk factors, appetite-regulating hormones, sex hormones, and PBMCs.		X		X		
Puberty status	Tanner stage		X		X		X
Sleep							
Actigraphy	Sleep duration, movements, and awakenings	X		X		X	
Polysomnography	Sleep stages, duration, latency, awakenings, and arousals		X		X		
Stanford Sleepiness Scale	Alertness		X		X		X
Sleep Screen Questionnaire-Children and Adolescents (SSQ-CA)	Sleep duration, latency, awakenings, and tiredness/sleepiness		X		X		X
Learning and brain function							
Track-It and word memory test	Learning ability, including skill learning ability and explicit memory		X		X		
EEG/EMG	Muscle activity during skill learning, corticocortical functional connectivity, and corticomuscular connectivity		X		X		
School performance	Mathematics proficiency and Danish reading comprehension		X		X		X
Motor skills							
Pegboard test and handgrip dynamometer	Fine motor skills and muscular strength (gross motor skills)		X		X		X
Lifestyle behaviors							
3-day dietary record	Total energy intake, energy percentage of carbohydrate, fat, protein, and fiber, and meal timing	X		X		X	
Meal timing diary	Eating window duration	X		X		X	
Actigraphy	Total physical activity and time spent on MVPA	X		X		X	

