#### Primary analysis

The effect of the intervention will be evaluated using linear mixed-effects models (LMMs) estimated with restricted maximum likelihood (REML), allowing inclusion of all available observations in the statistical model without imputations.

The LMMs will be performed with fixed effects for group, time, and the group-by-time interaction, with participant included as a random effect. The primary model will include baseline and 12-week measurements. An extended model with 3 time points (baseline, 12 weeks, and 6 months) will be developed to assess the sustainability of effects over the follow-up period. These models will be adjusted for stratification variables and baseline pubertal stage, included as fixed main effects. Model assumptions will be evaluated using residual diagnostics. If model assumptions are not met, appropriate transformations will be considered.

The primary analysis will be conducted using an intention-to-treat approach, including all randomized children according to their group allocation, regardless of whether or not they complete the study.

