#### Sensitivity analyses

Sensitivity analyses will be restricted to completers only and include a per-protocol analysis. This analysis will include only children from the sleep extension group who complete the study and extend their sleep by at least 30 min per night after 12 weeks. This amount of sleep extension is clinically relevant for outcomes related to body weight regulation and cognitive function (21, 30).

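### Ending participation for non-compliance, with no stated week-12 visit for children who stop the intervention, conflicts with the promised intention-to-treat analysis

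*Protocol article*

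**What the plan says.** Four statements in the protocol article bear on this.

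- **Ethics and dissemination**: "Participation will also be discontinued in cases of significant non-compliance, lack of cooperation, or unforeseen events that make the child ineligible to participate". What ends is participation, not only the intervention. The article gives no threshold or timing for significant non-compliance.
- **Data collection and outcomes**: "Participants who discontinue the intervention will be invited to attend an early termination visit". For withdrawal from the study, the text adds: "Participants who withdraw from the study during the active intervention will be invited to attend an early termination visit identical to Visit B". It does not say whether a child who stops the intervention, or is discontinued by the study, still attends at week 12 or week 38.
- **Primary analysis**: the approach is intention-to-treat, "including all randomized children according to their group allocation, regardless of whether or not they complete the study". The mixed model is chosen as "allowing inclusion of all available observations in the statistical model without imputations", and "The primary model will include baseline and 12-week measurements". Covariates are the stratification variables and baseline pubertal stage.
- **Compliance**: "Compliance is defined as an increase in sleep duration of ≥30 min/night after 12 weeks". The per-protocol analysis under Sensitivity analyses uses the same 30-minute threshold and is separate from the primary analysis.

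**The concern.** Intention-to-treat needs the week-12 outcome of every randomised child who is willing to give it, whether or not the child followed the assigned schedule. A conduct rule that ends participation for non-compliance works against this. It creates missing or early outcomes, and it does so according to something that happens after randomisation and may be related to outcome.

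The article's own Introduction gives reason to expect such a relation. In the earlier parallel trial of 78 children, body weight did not differ significantly between groups, yet across groups those who slept at least 30 minutes longer had a lower BMI z-score than those who did not.

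The effect is probably uneven between arms. The article's only definition of compliance, a gain of at least 30 minutes, is meaningful only for the extension arm, since controls are asked to keep their usual routine. Adherence is followed at the sessions, so removal before week 12 is practicable.

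Both co-primary outcomes are exposed. The planned sensitivity analyses (completers and per-protocol) select further in the same direction, so they would not reveal the problem. A later analysis plan cannot recover outcomes that were never collected.

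**Working it through.** **1. The plan's own figures.** None is in dispute. With d = 0.58, two-sided alpha 0.025 and 80% power, the normal approximation gives 57 per arm, or 114. Allowing for 20% dropout, 114/0.8 = 142.5, against the stated 142. The 0.52 BMI z-score units and the SD of 0.9 agree with d = 0.58 (0.52/0.9 = 0.578).

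**2. What happens to a removed child in the model.** Such a child has a baseline value and perhaps an early-visit value. The primary model has only two time points, baseline and week 12. Without a week-12 value, the child stays in the model through baseline, and the week-12 mean of the arm is in effect completed from retained children of the same arm with similar baseline and covariates. That is valid only if, given those variables, removal is unrelated to the week-12 outcome. Compliance is not in the model, so the condition fails if removal depends on compliance and compliance predicts outcome.

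**3. An early visit is not the same measurement.** It follows a shorter exposure. For learning, the article expects a repeated-administration effect at Visit B, and an early visit changes the retest interval.

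**4. Illustration when there is a true effect.** The article gives no removal rate, so p is assumed. Let a share p of the extension arm be removed, with no benefit and no week-12 value, let the rest have effect δ, and let no control be removed.

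- Intention-to-treat effect: (1−p)δ
- Effect estimated from those retained: δ
- Relative overstatement: 1/(1−p) − 1

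| p (assumed) | (1−p) × 0.52 | Overstatement |
|---|---|---|
| 0.04 | 0.499 | 1/0.96 − 1 = 4% |
| 0.10 | 0.468 | 1/0.90 − 1 = 11% |

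The value 0.04 borrows the upper bound of the dropout rate that the sample-size section reports from earlier sleep trials. It is not a rate of removal for non-compliance.

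**5. Illustration when there is no true effect.** The formula in step 4 gives no bias here. Bias then needs a further assumption: removed children would have done worse than retained ones by g SD after adjustment. The bias is p × g. With p = 0.10 and g = 0.2 to 0.5, this is 0.02 to 0.05 SD, or 0.018 to 0.045 BMI z-score units at SD 0.9. With 71 controls and 71 × 0.9 = 63.9 extension children, the standard error is √(1/71 + 1/63.9) = 0.172 SD. The nominal 0.025 test then runs at about 0.026 to 0.031.

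**The case against.** The case on the other side has real force.

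- **Outcomes are not simply lost.** The early visit for withdrawal in the active phase has the content of Visit B, so both co-primary outcomes can be measured, and removed children remain in the analysis through baseline. This stands. The difficulty is the timing and the purely voluntary attendance.
- **Ordinary non-compliers are evidently meant to stay.** The 30-minute criterion is judged only after 12 weeks. The per-protocol set requires both completion and a 30-minute gain, which presumes that some completers fall short. The exploratory analyses relate continuous change in sleep to outcome. Families in difficulty are offered adjustments. This also stands: significant non-compliance is a narrower, undefined event and may be rare.
- **It is not confined to one arm.** Controls also attend sessions and complete diaries, actigraphy, dietary records and urine collection, so lack of cooperation can arise there too. An excess in the extension arm is probable, not shown.
- **The 20% dropout must not be used as p.** It is an allowance for dropout from any cause across both arms, and the article calls it conservative. Putting it into the formula would give 1/0.8 − 1 = 25%, which a reader might take as the expected bias. The article does not support that.
- **Entry of early measurements into the model is commonly a matter for the analysis plan**, which is not shown. The point does not rest on that silence. It rests on a conduct rule that the article itself states.

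**Conclusion.** The conflict is real and should be resolved. The article ends participation for non-compliance or lack of cooperation and does not secure the week-12 visit for children who stop the intervention, while promising intention-to-treat on week-12 outcomes. Missing or early outcomes would then depend on compliance, and the primary estimate would be pulled toward a complier effect.

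The size cannot be computed from the documents. The figures of about 4% and 11% hold only for the assumed p, with no benefit in removed children, no week-12 data from them and no removals among controls. Bias in favour of the intervention is likely but not certain.

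A reader might go further and infer that non-compliers as a group lose their outcome, or that the intention-to-treat analysis is replaced by a complier analysis. The documents do not support this: early visits can collect both co-primary outcomes, all randomised children stay in the analysis set, and the complier comparison is kept as a separate sensitivity analysis.

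**What to change.** Reconcile Ethics and dissemination, Data collection and outcomes, and Primary analysis by separating discontinuation of the intervention from discontinuation of outcome collection. State that:

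1. children discontinued for non-compliance or lack of cooperation are still invited to Visit B at week 12 and Visit C at week 38, unless the child or family declines;
2. an early-termination measurement is not entered as the week-12 value in the primary model.

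When the intervention itself stops remains for the investigators, and the child's right to stop is unchanged.

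The cost is an amendment and some extra effort to schedule less motivated families. Visits B and C are already planned for every child.

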## Conclusion

More2Sleep is designed to determine the effect of a pragmatic sleep extension intervention on body weight regulation and learning ability in children who sleep less than the recommended for their age and sex.

This study will contribute evidence about the effects of sleep extension on children's health and well-being. The impact of this research is potentially considerable and multi-dimensional. In terms of research, this study may inspire future studies on sleep manipulation in childhood obesity, neurophysiology, and cognitive function. In terms of clinical practice, it may contribute to the development of sleep-based treatment strategies or inform future sleep recommendations for school-aged children. Perhaps more importantly, in terms of societal impact, this study has the potential to provide an easy way for parents to improve their children's body weight and learning abilities, which will accompany them for the rest of their lives.
